#### Hypotheses

The following two-tailed test problem is used for the primary outcome:

Hypothesis 0: beta1=0 versus Hypothesis 1: beta1≠0, where beta1 is the coefficient of the logistic regression model, and null hypothesis: H0. There is no correlation between a significant reduction in fecal calprotectin of 50% from baseline in Week 6 and clinical response to therapy with golimumab in Week 26.

Therefore, our research hypothesis, H1, is that there is a correlation between a significant reduction in fecal calprotectin of 50% from baseline in Week 6 and clinical response to therapy with golimumab in Week 26.

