### Statistics

#### Analysis

Our aim is to study the detection of a positive trough level of golimumab of >2.5 μg/ml and a significant reduction in fecal calprotectin of 50% from baseline in Week 6 as a reliable predictor for clinical response in Week 26 during long-term treatment with golimumab. In this connection, a level between 2.5 μg/ml and 4.3 μg/ml is regarded as being associated with a therapeutic effect of golimumab [8,9].

Statistical analysis is mainly carried out with descriptive methods such as frequency tables, and statistical parameters such as mean, standard deviation, and quantiles. Bar graphs are used for qualitative data and box-and-whisker plots for quantitative data. In addition, inferential statistical analysis is carried out with relevant significance tests and confidence intervals. Missing data are not imputed.

In order to evaluate the primary outcome, the test problem presented in the section on statistical hypotheses is formulated and solved. The test is carried out with a power of 80% and a two-tailed significance level of alpha=.05. Analysis is carried out with a logistic regression model based on the percentage change of fecal calprotectin and golimumab trough levels. In addition, secondary parameters (eg, ATGs, CRP, WBC) are also analyzed to identify further correlations between the data of Week 6 and therapy outcome in Week 26. The aim is to identify further constraints to the statistical model in order to take into account all relevant parameters in the final version of the algorithm. Secondary outcomes are assessed in an explorative way, that is, no pre-formulated hypotheses are tested. The *P* values obtained are thus interpreted according to Fisher’s method: a *P* value is considered a metric value, and the smaller the *P* value, the larger the significance of the corresponding effect. No interim analyses are planned. Data analysis is carried out only once, at the end of the study.

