### Sample Size

#### Rationale

Sample size is planned based on data from studies researching a correlation between fecal calprotectin and response to an anti-TNFα therapy.

De Vos et al [10] describe response rates as: “After 10 weeks anti-TNFα therapy induced endoscopic remission in 63% (confidence interval: 47–78%) of patients”. Molander et al [11] describe the correlation between the predictive quality of fecal calprotectin and the remission rate. The results are displayed in Table 1.

**Table 1 table1:** Cross classification of fecal calprotectin predictive quality and remission.

		Fecal calprotectin decline		Total
		Yes	No	
Remission				
	Yes	30	3	33
	No	6	21	27
Total		36	24	60

Based on these results, the odds ratio (OR) is calculated as OR (30*21) / (6*3)=35. It should be noted that for the above study the cut-off point for fecal calprotectin decline was a reduction of >75% from baseline. Lower cut-off points, for example, a 50% reduction, would lead to smaller OR, as the number of patients with neither decline nor response is described as being almost constant in the above-mentioned literature: “Absence of decrease in calprotectin levels at week 6 identified patients resistant to the treatment” [11]. It is therefore assumed for sample size calculation that 80% of the patients will have a “fecal calprotectin decline.” Table 2 summarizes the scenarios that have been taken into consideration.

**Table 2 table2:** Sample size rationale: Response rates and their effect on resulting OR for 9 different scenarios.

Scenario	Response rate (%)	OR
1	40	10
2	40	20
3	40	30
4	50	10
5	50	20
6	50	30
7	60	10
8	60	20
9	60	30

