#### Calculation

Sample size calculation is carried out with the statistical analysis software SAS. Table 3 shows the required number of evaluable patients for each scenario. It is expected that 5% of the intention-to-treat principle population will be excluded. Sample size is inversely proportional to the OR and the response rate.

**Table 3 table3:** Sample size calculation: Number of evaluable subject and total number of subjects considering dropouts for 9 different scenarios.

Scenario	Response rate, %	OR	Evaluable subjects, n	Subjects including potential dropouts, total n
1	40	10	58	61
2	40	20	40	42
3	40	30	34	36
4	50	10	50	53
5	50	20	34	36
6	50	30	29	31
7	60	10	45	48
8	60	20	31	33
9	60	30	26	28

To prevent study failure due to an underpowered study, a worst case scenario with a response rate of 40% and an OR of 10 is used as a basis for sample size. A total of 58 evaluable subjects are therefore necessary for the trial, thus 61 patients must be recruited.

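### At the plan's own design point, the cell of responders without calprotectin decline is empty in about a third of trials, so ordinary logistic regression gives no finite beta1 and a predicted probability of 0

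*Protocol article*

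**What the plan says.** - **Hypotheses.** The primary test is two-tailed, beta1=0 against beta1≠0, "where beta1 is the coefficient of the logistic regression model". The null is put in terms of a yes/no predictor: "There is no correlation between a significant reduction in fecal calprotectin of 50% from baseline in Week 6 and clinical response" to golimumab in Week 26. No test statistic or estimation method is named.
- **Analysis.** "The test is carried out with a power of 80% and a two-tailed significance level of alpha=.05". Confidence intervals are planned. The same section describes the logistic model as based on the percentage change in calprotectin together with golimumab trough levels.
- **Sample Size, Rationale.** "It is therefore assumed for sample size calculation that 80% of the patients will have a" calprotectin decline. This is again a binary predictor.
- **Sample Size, Calculation.** "a worst case scenario with a response rate of 40% and an OR of 10 is used as a basis for sample size", which gives 58 evaluable patients. "Sample size calculation is carried out with the statistical analysis software SAS"; the procedure and test are not given.
- **Study Objective.** The product is an algorithm that calculates the probability of Week 26 response from Week 6 data. The Discussion intends it to separate responders from non-responders.

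**The concern.** An 80/20 split of 58 patients puts about 12 in the smaller group. A large odds ratio makes response in that group rare. If none of them responds, the logistic likelihood keeps rising as beta1 grows. There is then no finite maximum-likelihood estimate and no upper limit for the odds ratio, and the fitted probability for the whole group is 0.

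Two things are at stake:
- **The estimate.** The trial exists to deliver predicted probabilities, and a fitted 0 from about 12 patients is not a usable prediction.
- **The test.** A test of a logistic coefficient is easily taken to be the Wald p value printed beside it. That statistic is uninformative when the cell is empty and weak when the cell is nearly empty.

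**Working it through.** **Inputs** (Analysis; Sample Size): N=58, decline 80%, response 40%, OR 10 (ln 10 = 2.303), two-sided alpha 0.05, power 80%.

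**1. Response probabilities.** The 40% can be read in two ways.
- *At the predictor mean:* intercept = ln(0.4/0.6) − 0.8 × 2.303 = −2.248. Response is 9.6% without decline and 51.4% with decline.
- *Overall rate:* solve 0.8·p1 + 0.2·p0 = 0.40 with OR 10. Response is 8.4% without decline and 47.9% with decline.

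**2. Reproducing Table 3.** A likelihood-ratio chi-square calculation (1 df, non-central), with the first reading and the null intercept at logit of the response rate, gives 58, 40, 34, 50, 34, 29, 45, 31, 26. All nine rows match. For scenario 1 the non-centrality per patient is 0.1359, so 58 × 0.1359 = 7.88 and power is 80.2% (57 patients give 79.5%). The asymptotic Wald formula does not match:

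n = (1.96 + 0.8416)² × [1/(0.8·p1(1−p1)) + 1/(0.2·p0(1−p0))] / 2.303²

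This is 7.849 × 62.85 / 5.302 = 93 on the first reading and 7.849 × 69.86 / 5.302 = 103 on the second.

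**3. The sparse cell.** Without decline: 0.2 × 58 = 11.6 patients. Expected responders among them: 11.6 × 0.0956 = 1.11, or 11.6 × 0.0842 = 0.98.

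**4. Probability that the cell is empty.** With group sizes random, it is (1 − 0.2·p0)^58:
- 0.9809^58 = 32.7% (at the mean);
- 0.9832^58 = 37.4% (overall rate).

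With exactly 12 patients without decline, (1 − p0)^12 gives 30.0% and 34.8%.

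**5. Exact power at N=58.** All 2×2 tables were enumerated, with the number without decline Binomial(58, 0.2). Size is at a common response rate of 40%. Non-finite fits count as non-rejections for Wald.

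| Test of beta1=0 | Power, 40% at mean | Power, 40% overall | Size |
|---|---|---|---|
| Wald | 39.9% | 31.2% | 3.1% |
| Ordinary likelihood ratio | 83.1% | 80.8% | 5.8% |
| Firth penalised likelihood ratio | 78.8% | 75.2% | 4.6% |
| Fisher exact | 73.0% | 69.2% | 3.3% |

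The ordinary likelihood-ratio test rejects in nearly all non-finite samples: 32.6 of 32.7 percentage points, and 37.2 of 37.4.

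**6. Example.** Take 0 of 12 responders without decline and 23 of 46 with decline.
- Maximum likelihood: OR infinite, predicted probability without decline 0.
- Likelihood ratio: 2 × [46·ln 0.5 − 23·ln(23/58) − 35·ln(35/58)] = 2 × (−31.88 + 38.95) = 14.1, against a critical value of 3.84. The test rejects clearly.
- Firth, which for a 2×2 table adds 0.5 to each cell: OR = (23.5 × 12.5)/(23.5 × 0.5) = 25, predicted probability without decline 0.5/13 = 3.8%.

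**The case against.** The strongest reply is that the article plans no Wald test. Beta1=0 can be tested by Wald, score, likelihood-ratio, exact or penalised methods. The only evidence of intent, Table 3, points to the likelihood ratio, and under that test the stated 80% is met. Test statistic, interval type and handling of sparse cells are usually left to the statistical analysis plan, which exists but is not shown.

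Most of this stands. A reader might infer that the planned test has 31-40% power, or that the primary analysis fails outright in a third of trials. The documents support neither. The first figure belongs to a test they do not name, and an infinite estimate does not stop a likelihood-ratio test from rejecting. The unnamed statistic is not itself the defect.

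A second reply is that the Analysis section describes percentage change plus trough level, not one dichotomy. This limits the result. With a continuous percentage change, the empty-cell and power figures do not apply as computed, but neither does Table 3, which was sized on a binary predictor. Adding trough level beside a binary decline would not remove the problem: if no patient without decline responds, beta1 is still not finite.

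What neither reply answers is estimation. Choosing the likelihood-ratio test rescues the p value, but not the odds ratio or the predicted probabilities that are the stated aim.

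**Conclusion.** The concern holds as a problem of estimation, with a conditional risk for the test. At the sponsor's own design point, a logistic coefficient fitted by ordinary maximum likelihood is not finite in 33-37% of trials, and the algorithm then assigns probability 0 to everyone without decline. The stated 80% power is sound for an ordinary likelihood-ratio test (81-83% exact, size slightly above nominal at 5.8%). It would fall to about 31-40% only if a Wald coefficient p value were reported.

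The result assumes a binary 50% reduction, 80% decline, OR 10 and 58 evaluable patients; the ranges cover both readings of the 40% response rate. The full analysis plan may already deal with part of this. The change should be made, because it is cheap and protects the trial's main product.

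**What to change.** 1. State that beta1 and the predicted probabilities are estimated by Firth penalised logistic regression, with a profile penalised-likelihood 95% CI.
2. State that beta1=0 is tested by a likelihood-ratio test and not by Wald. If the penalised likelihood-ratio test is chosen, restate power at 58 as about 75-79%. If the ordinary one is kept, the 80% stands.
3. Reconcile the Analysis section (percentage change plus trough level) with Hypotheses and Sample Size (binary 50% reduction). If the primary predictor is continuous, Table 3 and the figures here need to be redone.

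The cost of items 1 and 2 is a short statement in the analysis plan and one procedure option, with somewhat lower stated power if the penalised test is used. No extra patients are needed unless the sponsor wants 80% with that test. The data are analysed only once, at the end, so the choice should be fixed before then.

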### Sample Size

#### Rationale

Sample size is planned based on data from studies researching a correlation between fecal calprotectin and response to an anti-TNFα therapy.

De Vos et al [10] describe response rates as: “After 10 weeks anti-TNFα therapy induced endoscopic remission in 63% (confidence interval: 47–78%) of patients”. Molander et al [11] describe the correlation between the predictive quality of fecal calprotectin and the remission rate. The results are displayed in Table 1.

**Table 1 table1:** Cross classification of fecal calprotectin predictive quality and remission.

		Fecal calprotectin decline		Total
		Yes	No	
Remission				
	Yes	30	3	33
	No	6	21	27
Total		36	24	60

Based on these results, the odds ratio (OR) is calculated as OR (30*21) / (6*3)=35. It should be noted that for the above study the cut-off point for fecal calprotectin decline was a reduction of >75% from baseline. Lower cut-off points, for example, a 50% reduction, would lead to smaller OR, as the number of patients with neither decline nor response is described as being almost constant in the above-mentioned literature: “Absence of decrease in calprotectin levels at week 6 identified patients resistant to the treatment” [11]. It is therefore assumed for sample size calculation that 80% of the patients will have a “fecal calprotectin decline.” Table 2 summarizes the scenarios that have been taken into consideration.

**Table 2 table2:** Sample size rationale: Response rates and their effect on resulting OR for 9 different scenarios.

Scenario	Response rate (%)	OR
1	40	10
2	40	20
3	40	30
4	50	10
5	50	20
6	50	30
7	60	10
8	60	20
9	60	30

#### Calculation

Sample size calculation is carried out with the statistical analysis software SAS. Table 3 shows the required number of evaluable patients for each scenario. It is expected that 5% of the intention-to-treat principle population will be excluded. Sample size is inversely proportional to the OR and the response rate.

**Table 3 table3:** Sample size calculation: Number of evaluable subject and total number of subjects considering dropouts for 9 different scenarios.

Scenario	Response rate, %	OR	Evaluable subjects, n	Subjects including potential dropouts, total n
1	40	10	58	61
2	40	20	40	42
3	40	30	34	36
4	50	10	50	53
5	50	20	34	36
6	50	30	29	31
7	60	10	45	48
8	60	20	31	33
9	60	30	26	28

To prevent study failure due to an underpowered study, a worst case scenario with a response rate of 40% and an OR of 10 is used as a basis for sample size. A total of 58 evaluable subjects are therefore necessary for the trial, thus 61 patients must be recruited.

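### Table 3 labels its input a response rate, but 58 patients match 40% only as the probability at the predictor mean (43% overall); at 40% overall, power is about 76-78%

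*Protocol article*

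**What the plan says.** The Rationale section says it is "assumed for sample size calculation that 80% of the patients will have a" calprotectin decline. Tables 2 and 3 cross response rates of 40, 50 and 60% with odds ratios of 10, 20 and 30. Under Calculation, "Table 3 shows the required number of evaluable patients for each scenario", and the design point is named: "a worst case scenario with a response rate of 40% and an OR of 10 is used as a basis for sample size". That gives 58 evaluable and 61 recruited patients, chosen so that the study is not underpowered.

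Under Analysis, "The test is carried out with a power of 80% and a two-tailed significance level of alpha=.05", and "Analysis is carried out with a logistic regression model". Under Hypotheses the test is "Hypothesis 0: beta1=0 versus Hypothesis 1: beta1≠0, where beta1 is the coefficient of the logistic regression model", with the 50% calprotectin reduction as the predictor. On method, the article says only that "Sample size calculation is carried out with the statistical analysis software SAS"; it names no procedure or parametrisation. On dropout: "It is expected that 5% of the intention-to-treat principle population will be excluded".

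**The concern.** A reader takes a response rate to be the share of all patients who respond. The Rationale supports that reading, because it starts from observed population figures (63% endoscopic remission in one cited study, 33 of 60 in Table 1). With the overall rate, the odds ratio and the share with decline all given, the two group response probabilities are fixed and the sample size can be checked. The check does not return 58.

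What is at stake is the power claim at the scenario presented as the worst case. If the scenario actually computed had a higher overall response rate than the one named, the stated 80% applies to a milder case.

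**Working it through.** **Inputs.** Two-sided alpha 0.05 and power 80% (Analysis); logistic test of beta1 (Hypotheses); decline in 80% (Rationale); rate r = 40% and OR = 10 (Calculation); 5% excluded (Calculation).

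**Formula.** The predictor is binary with prevalence 0.8. The logit is a without decline and a + ln(OR) with decline. For the likelihood-ratio (LR) test on 1 df, the noncentrality per patient is

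d = 2 × Σ w × [p(θ − θ*) − (log(1+e^θ) − log(1+e^θ*))],

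summed over the two groups with weights w = 0.2 and 0.8. Here θ is the group logit, p its probability and θ* the logit under the null. Power of 80% needs n × d = 7.849.

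**Step 1: reproduce the protocol's figure.** Take 40% as the probability at predictor value 0.8.
- a = logit(0.40) − 0.8 × ln 10 = −0.4055 − 1.8421 = −2.2475, so response is 9.56% without decline.
- a + ln 10 = 0.0551, so response is 51.38% with decline.
- With θ* = logit(0.40), d = 0.13593 and n = 7.849/0.13593 = 57.7, so **58**.

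Across the nine scenarios this gives 58, 40, 34, 50, 34, 29, 45, 31, 26, which is Table 3 exactly.

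**Step 2: the overall rate this implies.** 0.2 × 9.56% + 0.8 × 51.38% = **43.0%**. At OR 20 and 30 the 40% rows imply 45.0% and 46.3%.

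**Step 3: make 40% the overall rate.** Solving 0.2 × p0 + 0.8 × p1 = 0.40 with OR 10 gives a = −2.3868, p0 = 8.42% and p1 = 47.90%.

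| Null convention | d | n × d at 58 | Power at 58 | n for 80% |
|---|---|---|---|---|
| Mean linear predictor, as in step 1 | 0.12747 | 7.393 | 77.6% | 61.6, so 62 |
| Overall rate, logit(0.40) | 0.12286 | 7.126 | 76.1% | 63.9, so 64 |

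A two-proportion formula gives about 62.5 patients in total and a Wald calculation 104. Placing the 40% in the no-decline group gives 45; placing it in the decline group gives 78. None of these returns 58.

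**Step 4: exact enumeration** at n = 58, overall rate 40%, OR 10: Pearson chi-square 76.5%; uncorrected LR test 80.8%, but with an actual type I error of about 5.8%.

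**Step 5: power at 43.0% overall.** 80.2% under Table 3's null convention; 79.1% (n = 60 for 80%) with the null at the overall rate.

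**Step 6: the table with the rate read as overall.**

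| Rate | Table 3 (OR 10/20/30) | Table 3's null | Overall-rate null |
|---|---|---|---|
| 40% | 58/40/34 | 62/45/39 | 64/49/44 |
| 50% | 50/34/29 | 51/37/32 | 52/38/33 |
| 60% | 45/31/26 | 45/31/27 | 45/31/27 |

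**Step 7: dropout.** If 5% of those recruited are excluded, recruited n = evaluable n/0.95. 58/0.95 = 61.05, so 62 (61 × 0.95 = 57.95). The printed 61 agrees with 58 × 1.05 = 60.9 rounded up. Scenario 2: 40/0.95 = 42.1, so 43, not 42. The other seven rows are unchanged.

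**The case against.** The parametrisation is inferred, since the article names only the software, and a journal article may leave such detail to the full protocol. That stands as a caution. But nine exact matches out of nine are strong evidence, and the point does not rest on the inference alone: the printed assumptions do not give 58 under any of the overall-rate calculations tried.

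A reader might infer that true power is simply 76%. That is one end of a range. Changing only the meaning of 40% and keeping Table 3's null convention gives 77.6% and 62 patients; the 76.1% and 64 also change the null. The enumerated LR test still exceeds 80%, though at a size of about 5.8% rather than the stated 5%. Fisher's exact test would show 69.2%, but the protocol does not name it, so that figure should not be used to enlarge the problem.

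A reader might also infer that the wrong worst case was chosen. The recomputation does not support this: scenario 1 has the smallest error of the three 40% scenarios (4 to 6 patients) and is still the largest of the nine after correction. Finally, the planning values are round assumptions, and three points of response rate are small beside the cited remission interval of 47-78%. That limits the importance of the point. It does not make the printed power figure follow from the printed inputs.

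**Conclusion.** The point holds in a limited form. Table 3 is internally consistent but its input is mislabelled: the tabulated rate behaves as the probability at the predictor mean, which is 43.0% overall in the scenario used for sizing. At a true overall rate of 40%, 58 evaluable patients give about 76-78% power, a shortfall of about 2.5 to 4 percentage points or 4 to 6 evaluable patients. This rests on OR 10, 80% decline, a single binary predictor, two-sided alpha 0.05 and a test that holds its size. The dropout slip is real but separate, and affects scenarios 1 and 2 by one patient each. The documents do not support calling the design seriously underpowered or the choice of scenario wrong.

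**What to change.** - State in the Sample Size section, and in the labels of Tables 2 and 3, that the tabulated rate is the response probability at the predictor mean, equal to 43% overall in scenario 1.
- Restate the power of 58 evaluable patients as about 76-78% at an overall rate of 40% and about 79-80% at 43%, for OR 10 and 80% decline.
- Give the 40% and 50% rows for an overall rate under one stated null convention: 64/49/44 and 52/38/33 with the overall-rate null, or 62/45/39 and 51/37/32 with the null that Table 3 uses. In the 60% row only the OR 30 entry moves, from 26 to 27.
- Compute the dropout column as n/0.95. At the tabulated n this changes scenario 1 from 61 to 62 and scenario 2 from 42 to 43; carry the 62 into Trial Design and Calculation.

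The cost is a corrected table and a slightly less favourable stated power. No added evaluable patients are requested; the recruitment target moves by one.

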### Study Population

The evaluation of primary and secondary outcomes is carried out according to the intention-to-treat principle. The corresponding population comprises all patients included in the study regardless of possible protocol violations (eg, dropouts). In addition to intention-to-treat analysis, sensitivity analysis according to the per-protocol principle is carried out. Relevant protocol violations leading to exclusion from the per-protocol group are defined in the statistical analysis plan.

